## Abstract

**Background:**

A Personal Health Record (PHR) is an online application that allows patients to access, manage, and share their health data. PHRs not only enhance shared decision making with healthcare providers, but also enable remote monitoring and at-home-collection of detailed data. The benefits of PHRs can be maximized in insulin dose adjustment for patients starting or intensifying insulin regimens, as frequent self-monitoring of glucose, self-adjustment of insulin dose, and precise at-home data collection during the visit-to-visit period are important for glycemic control. The aim of this study is to examine the efficacy and safety of insulin dose adjustment based on a smartphone PHR application in patients with diabetes mellitus (DM) and to confirm the validity and stability of an information and communication technology (ICT)-based centralized clinical trial monitoring system.

**Methods:**

This is a 24-week, open-label, randomized, multi-center trial. There are three follow-up measures: baseline, post-intervention at week 12, and at week 24. Subjects diagnosed with type 1 DM, type 2 DM, and/or post-transplant DM who initiate basal insulin or intensify their insulin regimen to a basal-bolus regimen are included. After education on insulin dose titration and prevention for hypoglycemia and a 1-week acclimation period, subjects are randomized in a 1:1 ratio to either an ICT-based intervention group or a conventional intervention group. Subjects in the conventional intervention group will save and send their health information to the server via a PHR application, whereas those in ICT-based intervention group will receive additional algorithm-based feedback messages. The health information includes level of blood glucose, insulin dose, details on hypoglycemia, food diary, and step count. The primary outcome will be the proportion of patients who reach an optimal insulin dose within 12 weeks of study enrollment, without severe hypoglycemia or unscheduled clinic visits.

**Discussion:**

This clinical trial will reveal whether insulin dose adjustment based on a smartphone PHR application can facilitate the optimization of insulin doses in patients with DM. In addition, the process evaluation will provide information about the validity and stability of the ICT-based centralized clinical trial monitoring system in this research field.

**Trial registration:**

Clinicaltrials.gov NCT 03112343. Registered on 12 April 2017.

**Electronic supplementary material:**

The online version of this article (doi:10.1186/s12911-017-0507-4) contains supplementary material, which is available to authorized users.

## Background

Despite the development of various diabetes medications, insulin therapy is still the only effective treatment not only in patients with type 1 diabetes mellitus (T1DM), but also in patients with advanced type 2 diabetes mellitus (T2DM) that is inadequately controlled by oral glucose-lowering agents due to disease progression [1–3]. However, due to the failure of insulin dose titration and fear of hypoglycemia, insulin treatment is perceived as a complex and reluctant therapy by both patients and doctors [4, 5]. To overcome these barriers, frequent and intensive self-monitoring of glucose and detailed feedback on insulin dosage are critical [6]. Therefore, there is a strong clinical need for a technological approach to enhance the timely communication between patients and their healthcare providers about insulin therapy. Several studies have reported the efficacy of telephone counseling or text messaging based on paper-based collection of self-monitored glucose data [7], rather than automatic transmission of glucose data [8]. In contrast, there have been several randomized controlled trials of bolus-calculator applications in patients with T1DM [9]. However, most of these studies used applications without automatic data uploading functionality [10], and there have been continuous concerns regarding the safety of bolus calculator applications [9]. Until the safety of automated insulin dose calculator applications is sufficiently documented, there is a clinical need for mobile applications to enhance patient education around insulin dose adjustment.

A personal health record (PHR) is an online application that allows patients to access, manage, and share their own health data [11]. Unlike in self-care medical applications, focusing on incomplete self-care data, providing little useful information to clinicians, PHR not only enhances shared decision making with healthcare providers in actual clinical practice, but also enables remote monitoring and at-home-collection of detailed data in clinical trials [12]. These benefits of PHRs in both clinical practice and trials can be maximized in the education of insulin dose adjustment for patients with DM who are starting or intensifying their insulin regimen, as frequent self-monitoring of glucose level, self-adjustment of insulin dose, and at-home data collection with minimized visits to the hospital are important for description of details on glycemic control, including hypoglycemia, diet, and activity. However, the role of PHR in patients starting or intensifying insulin therapy has received less attention than in patients with early-stage T2DM, despite the strong clinical need for PHR in patients with T1DM or insulin-treated T2DM.

The aim of this study is to examine the efficacy and safety of insulin dose adjustment education based on a smartphone PHR in patients with DM who initiate or intensify their basal insulin regimen and to confirm the validity and stability of the information and communication technology (ICT)-based centralized clinical trial monitoring system by analyzes using PHR- and questionnaire-based evaluation.

## Methods

### Hypotheses

Our primary hypothesis is that the ICT-based intervention group will produce a greater proportion of patients who reach optimal insulin dose within 12 weeks compared with the conventional intervention group. Our secondary hypothesis is that the ICT-based intervention group will have a greater proportion of patients who reach HbA1c <7% without severe hypoglycemia at weeks 12 and 24, improved glycometabolic control (including levels of fasting glucose, HbA1c, lipid parameters, body weight, lean body mass, fat mass, and blood pressure), step count, exchange units for each food category, and fewer hypoglycemic events or acute complications relative to the conventional intervention group.

### Study design

This is a 24-week, open-label, randomized, multi-center ICT-based clinical trial conducted in two different university-affiliated hospitals, Samsung Medical Center and Samsung Changwon Hospital. There are three follow-up measures: baseline, post-intervention at week 12, and at week 24. Subjects diagnosed as T1DM, T2DM, and/or post-transplant DM who are initiating basal insulin or intensifying their insulin regimen to a basal-bolus regimen will be given education on insulin injection, dose adjustment, and prevention of hypoglycemia and will be provided a Bluetooth-enabled glucometer at visit 1 for screening. Subjects will receive instructions to measure daily glucose level using a home glucometer, to record insulin regimen and dose, complete the hypoglycemia diary in the application if blood glucose <70 mg/dL or a hypoglycemic event occurs, and to synchronize data so it automatically transfers to the system. Subjects who synchronized their information daily during a 1-week run-in period will be accepted into the clinical trial and randomly assigned to either the ICT-based intervention group or the conventional intervention group at a ratio of 1:1. After randomization during week 1, telephone counselling will be provided for re-instructing insulin dose adjustment and re-confirming participants’ use of the at-home measurement device and PHR applications (visit 2; televisit). Subjects in the ICT-based intervention group will receive algorithm-based feedback messages when their glucose levels are out of the target range, in addition to recording, saving, and sending their data to the server via PHR applications. Subjects in the conventional intervention group will only record, save, and send their data to the server via PHR applications, without feedback messages. Investigators will examine the saved health information, including level of blood glucose, insulin dose, details on hypoglycemia recorded in the hypoglycemia diary, food diary, and number of steps, transferred through the PHR applications. At each clinical visit, anthropometric parameters, current medication use including insulin dose and other glucose-lowering agents, vital signs, body composition, and a questionnaire assessing satisfaction with the investigation will be examined, and blood tests will be performed. Figure 1 shows an overview of the study.

**Fig. 1 Fig1:**
[figure not shown]
Information and communication technology-based centralized monitoring system. The CRC registers the subject in the integrated management system, registers personalized conditions such as target blood glucose, and logs in the personal health record app through the newly created user ID and password. The PHR app sends login information to the home monitoring system and returns the survey ID. The home monitoring system receives user information (personal information, screening number, etc.) from the integrated management system. The PHR app sends login information and survey ID to the hospital monitoring system and automatically registers the patient. The CRC registers personalized conditions, such as target blood glucose and subject classification, in the hospital monitoring system. Blood glucose values by glucometer, step count by Samsung Health app, insulin regimen, hypoglycemia diary, and food diary inputted by the patient are transmitted to the home and hospital monitoring systems through the HL7 v2 message. Based on the received blood glucose values, the hospital monitoring system sends an algorithm-based feedback message, and the PHR app shows the feedback message. The PHR app that receives the feedback message transmits the HL7 v2 message to the home monitoring system. All information and feedback messages saved in the home monitoring system are stored in the eCRF. ﻿*CRC* Clinical research coordinator, *PHR* Personal health record

### ICT-based centralized clinical trial monitoring system

A centralized clinical trial monitoring system based on ICT allows the investigators to store and retrieve personal medical information transmitted from a medical device at an out-of-hospital location (e.g., at home) and to obtain reliable clinical data. This system is expected to be useful for clinical decision making (Fig. 2). The ICT-based centralized clinical trial monitoring system for clinical trials used in this trial consists of 1) a PHR application that acts as a gateway to identify the subjects of the clinical trial and transmit biometric information to the server; 2) at-home measurement device (Bluetooth-enabled blood glucometer); 3) a home monitoring system server where transmitted data is stored, monitored, and transferred; 4) an electronic case report form (eCRF) system (EDC) that extracts and implements the data necessary for clinical trials from the home monitoring system data; and 5) an integrated management server, in which all the above data are collected and managed. The at-home measurement device required for this clinical trial is a blood glucometer linked with Bluetooth, which measures and transmits blood glucose levels to the PHR application with every measurement. Therefore, syncing to the PHR application with Bluetooth is required to save and transmit data to the server automatically. The step count taken per day acquired by the Samsung Health application (Samsung Electronics, Korea) is automatically linked to the PHR application. The Android-based ‘PHR app,’ having recently developed new functions making it capable of interoperability with a wide range of devices, transmission of PHR data to a clinical trial server, and a graphic interface for providing information to medical staff, will be applied for this clinical trial. In addition, subjects can record their insulin protocol, food diary, and ‘hypoglycemia diary’ in the PHR app. The home monitoring system accumulates transferred biometric data, including blood glucose levels measured from the at-home measurement device, step count, and recorded data, including insulin regimen, food diary, and hypoglycemia diary for each registered subject through an integrated management system and transmits the data to the eCRF system via HL7 v2 message, a standardized protocol. For the ICT-based intervention group, PHR app information is sent to the investigator web page in the home monitoring system, and the investigator can view the subject’s data. In addition, algorithm-based feedback messages are transmitted to investigators, as well as subjects in the ICT-based intervention group when blood glucose level is not within the target range. Push feedback messages generated by the home monitoring system server will be displayed on the screen of the subject’s PHR app. eCRF is necessary for inputting and storing clinical trial data for each visit per subject through the integrated management system. Only the investigator or designated person can access the eCRF system to input, store, and examine a subject’s data. The Clinical trial management system (CTMS) is a superordinate system for managing all data, from subject registration and randomization, for transmitting data to the home monitoring system and eCRF and for integrating and managing all data for each measurement per subject. In addition, the CTMS is responsible for the management of participating institutions and investigators, monitoring, and adverse reaction monitoring and reporting. For system data security, the PHR app, the investigator web page, the home monitoring system, the eCRF system, and the integrated CTMS all protect personal medical information and maintain high standards of confidentiality by system log recording methods through automatic logoff, control and authentication on access, data encryption, and data audits.

**Fig. 2 Fig2:**
[figure not shown]
Study flow chart

### Participants

#### Eligibility criteria

The inclusion criteria are as follows: 1) age between 18 and 69 years; 2) diagnosis of T1DM, T2DM, and/or post-transplant DM (post-transplant DM includes both individuals diagnosed with T1DM or T2DM before organ transplantation and those first diagnosed with DM after organ transplantation); 3) initiation or intensification of insulin regimens, including once-daily basal insulin (including initiation of basal insulin only or basal insulin plus rapid-acting insulin 1 to 3 times per day and intensification to multiple insulin injections from twice-daily premixed insulins or once-daily basal insulin; patients will be eligible unless the insulin regimen was initiated more than 1 month prior to study participation, with insulin dose adjustment education provided by registered diabetes educators); 4) most recent hemoglobin A1c (HbA1c) ≥8.0% based on the National Glycohemoglobin Standardization Program (NGSP) at least 3 months prior to participation (recent HbA1c values measured <3 months prior to screening are permitted); and 5) use of an Android-based smartphone manufactured by Samsung Electronics (Seoul, Republic of Korea; Galaxy S4 or later). Exclusion criteria include the following: 1) initiating twice-daily pre-mixed or intermediate-acting insulin therapy; 2) use of an insulin pump; 3) history of alcohol or drug abuse 1 year prior to participation; 4) history of psychological disorder (e.g., schizophrenia, depression, or bipolar disorder); 5) history of severe visual or hearing impairment; 6) history of active malignancy; 7) pregnancy; and 8) any condition, in the investigator’s opinion, not suitable for enrollment eligibility.

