The secondary outcome will be the proportion of patients who reach HbA1c <7% without severe hypoglycemia (unrecoverable hypoglycemia without the help of others) at weeks 12 and 24. Other secondary outcomes include mean fasting blood glucose values for three consecutive days prior to weeks 12 and 24; levels of HbA1c at weeks 12 and 24; the proportion of patients having hypoglycemia (total, asymptomatic, daytime, nighttime, severe hypoglycemia, and coma/convulsions) at weeks 12 and 24; the number of steps taken during weeks 1–12 and weeks 13–24; recorded exchange unit by food group (grain, fish, vegetable, fat, milk, and fruit groups) in each breakfast, lunch, and dinner on 3-day food diary at weeks 12 and 24; daily insulin dose, body weight, and blood pressure at weeks 12 and 24; lipid profiles including total cholesterol, high-density lipoprotein (HDL) cholesterol, triglycerides, and low-density lipoprotein (LDL) cholesterol at weeks 12 and 24; body composition, including lean body mass and fat mass, at weeks 12 and 24; satisfaction evaluation by Diabetes Treatment Satisfaction Questionnaire (DTSQ) [13–16] and a questionnaire for ICT-based centralized clinical trial monitoring at weeks 12 and 24; the number of self-monitoring blood glucose measurements; the mean duration of medical consultations by doctors at the outpatient clinic; and the number and mean duration of telephone counselling by diabetes educators at weeks 12 and 24.

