### Laboratory tests

At visits 1, 3, and 4, blood samples are collected after at least 8 h of fasting to determine fasting glucose, HbA1c, white blood cell count (WBC), hemoglobin, hematocrit, platelet count, total protein, albumin, globulin, blood urine nitrogen (BUN), creatinine, uric acid, total bilirubin, aspartate aminotransferase (AST), alanine transaminase (ALT), alkaline phosphatase (ALP), calcium, phosphate, total cholesterol, triglycerides, HDL cholesterol, and LDL cholesterol. At visit 1, a urine hCG test is performed as a pregnancy test in women with childbearing potential.

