### Education on insulin injection, dose titration, and prevention of hypoglycemia

At the screening visit (visit 1), all subjects are given face-to-face education on insulin injection, dose titration, and prevention of hypoglycemia. The initial daily basal insulin dose will be 10 units per day or 0.1–0.2 units per kg of body weight. The initial daily basal insulin dose can be increased when the fasting blood glucose level is 250 mg/dL or more at initiation, but it should not exceed 0.3 units per kg per day. The initial pre-prandial rapid-acting insulin dose will be 4 units or 0.1 unit per kg or 10% of the basal insulin dose. For patients who have already used insulin before enrollment, they will start on their previous insulin dose and adjust from there. Subjects in the study are instructed to titrate their insulin dose based on the glycemic target of fasting glucose 80–130 mg/dL in the morning, for those who are under 65 years of age and do not have a history of severe hypoglycemia that cannot be recovered without help. The target of fasting glucose level 100–140 mg/dL in the morning will be applied for subjects with 1) history of severe hypoglycemia; 2) age ≥ 65 years; 3) duration of diabetes mellitus over 15 years; 4) decreased renal function (estimated glomerular filtration rate < 45 mL/min/1.73 m^2^); 5) BMI <18.5 kg/m^2^; 6) unawareness of hypoglycemia; 7) unpredictable changes in blood glucose level; and 8) difficulties understanding the education provided.

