### Interventions

#### Randomization

Educators provide telephone counseling after the 1-week run-in period. Before the telephone counseling, investigators check the synchronization of the at-home measurement device and the PHR application through the web page for administrators. For those who are suitable for the clinical trial based on daily synchronization, block randomization will be performed. The subjects will be randomly allocated to an intervention with ICT-based centralized monitoring or not, at a ratio of 1:1, per the Interactive Web Response System (IWRS). The randomization is stratified according to the research institute (Samsung Changwon Hospital: Samsung Medical Center = 20:76) and the use of pre-prandial insulin two or more times per day.

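### The HbA1c entry criterion contradicts itself on timing and does not say whether the visit 1 HbA1c is the value that must be at least 8.0%

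*Protocol article*

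**What the plan says.** All references are to the protocol article.

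- **Eligibility criteria, inclusion 4.** The value that counts is the "most recent hemoglobin A1c (HbA1c) ≥8.0" percent (NGSP), dated "at least 3 months prior to participation (recent HbA1c values measured <3 months prior to screening are permitted".
- **Eligibility criteria, inclusion 3.** Insulin may already be under way at entry: "patients will be eligible unless the insulin regimen was initiated more than 1 month prior to study participation".
- **Laboratory tests.** "At visits 1, 3, and 4, blood samples are collected after at least 8 h of fasting to determine fasting glucose, HbA1c", among other tests. Visit 1 is the screening visit, as the section on education shows: "At the screening visit (visit 1), all subjects are given face-to-face education on insulin injection, dose titration, and prevention of hypoglycemia".
- **Randomization.** After the 1-week run-in the stated condition is technical: "For those who are suitable for the clinical trial based on daily synchronization, block randomization will be performed". No HbA1c check is mentioned at this step.
- **Outcome variables.** The secondary outcome named first is "the proportion of patients who reach HbA1c <7% without severe hypoglycemia", at weeks 12 and 24. HbA1c level at the same weeks is also a secondary outcome.
- **Data analysis.** Secondary outcomes are compared by chi-square or Fisher's exact test, or by t-test or rank-sum test. A stratified comparison uses site and pre-prandial insulin use. HbA1c above 9% is a prespecified subgroup.

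**The concern.** An HbA1c threshold at entry is there to select patients whose control is poor when they join. It does so only if the date of the qualifying value is fixed. Here the time clause points towards older values and then admits recent ones, so it fixes nothing. The article also collects an HbA1c at screening without giving it a stated role in eligibility.

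Three things are at stake, all secondary:

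1. A patient already below 7% at visit 1 could count as reaching that target without any change.
2. Wider spread in baseline HbA1c adds noise to comparisons of later HbA1c levels when the named tests do not take the baseline into account.
3. The two hospitals could follow different rules, and both could claim to comply.

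**Working it through.** **Does anything in the sample size depend on this?** The article's figure can be reproduced without HbA1c. Inputs from Sample size assumptions: 88% v 55%, two-sided alpha 0.05, power 90%. With pooled variance under the null:

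- mean proportion = (0.88 + 0.55)/2 = 0.715
- 1.960 × √(2 × 0.715 × 0.285) = 1.251
- 1.282 × √(0.88 × 0.12 + 0.55 × 0.45) = 0.762
- n = (1.251 + 0.762)² / 0.33² = 37.2, rounded up to 38 per group, as stated
- 38 / (1 − 0.20) = 47.5, rounded up to 48 per group, 96 in total, as stated

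The proportions refer to reaching the optimal insulin dose. That outcome is defined by glucose values, hypoglycemia, dose stability, correction doses and clinic visits. HbA1c does not enter.

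**What does the time window exclude?** Let *a* be the age of the HbA1c at screening and *d* the time from screening to participation (*d* ≥ 0; the article does not define participation).

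- Main clause: *a* + *d* ≥ 3 months.
- Parenthesis: *a* < 3 months.
- If either is enough, which is what permitting the second implies, every *a* qualifies. A value with *a* ≥ 3 months meets the first, and any other meets the second.
- If both had to hold, *a* would have to lie between 3 months − *d* and 3 months. That window is empty when *d* = 0 and about one week wide if participation means randomization after the run-in. This cannot be intended.
- If the main clause was meant to read as a maximum of three months, the parenthesis adds almost nothing. The article does not confirm that reading.

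**Which value qualifies?** The criterion relies on the latest value. The visit 1 sample is drawn at screening, before run-in and randomization. There are two readings:

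- If the visit 1 result counts as the latest value, anyone below 8.0% at visit 1 fails the criterion.
- If only values from before screening count, a patient can qualify on an earlier value and be below 8.0% at visit 1. Up to a month of insulin before entry makes some fall plausible.

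None of the sections listed above chooses between the two.

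**How large could the effect be?** The documents give no figure, so every input here is assumed. Suppose a share *s* of each arm is already below 7% at visit 1 and stays there without severe hypoglycemia, and the rest reach the target at 40% v 20%. The observed rate is *s* + (1 − *s*)*p*, so the difference is (1 − *s*) × 20 points.

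| Assumed *s* | Arm at 40% | Arm at 20% | Difference |
|---|---|---|---|
| 0% | 40% | 20% | 20 points |
| 10% | 0.10 + 0.90 × 0.40 = 46% | 0.10 + 0.90 × 0.20 = 28% | 18 points |
| 20% | 0.20 + 0.80 × 0.40 = 52% | 0.20 + 0.80 × 0.20 = 36% | 16 points |

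This shows only the direction and scale of the dilution. It is not an estimate for this trial.

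**The case against.** The case for leaving this alone has real force.

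- **Only the latest value counts.** A reader might infer that any old HbA1c of 8% or more is a ticket of entry. It is not: an old value cannot be used when a newer recorded one is below 8%. This stands.
- **Entry below 8% is not shown.** A reader might infer that such patients do enter, or that the visit 1 result is irrelevant to eligibility. The article is silent on the point, and on one natural reading the visit 1 result excludes them. This stands, but the silence is itself what needs repair.
- **Other criteria also select.** Patients must be starting or intensifying insulin, with the regimen begun no more than a month earlier, and the investigator may exclude anyone unsuitable. Nothing in the article suggests that patients near 7% are a material group, so the claim that selection fails is not supported. This stands.
- **No bias between arms.** The same rule applies to everyone before 1:1 allocation, and both randomization and analysis are stratified by site. Different readings at the two hospitals would leave the arms comparable within each. This stands; what remains is a less clearly defined population.
- **It is probably a slip of wording.** That may be so, but the article does not confirm it, and an eligibility rule has to be applied as written.
- **Baseline adjustment belongs in an analysis plan.** Its absence from the article is not a fault. It is proposed below because the article names tests that do not use the visit 1 HbA1c, and that value is already collected.

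**Conclusion.** The point holds in a limited form. As written, inclusion criterion 4 sets no limit on the age of the qualifying HbA1c, counts from two reference dates, and leaves open whether the visit 1 result must itself be 8.0% or more. Enrolment of patients below 8% at visit 1 is possible, not demonstrated.

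The reach is the HbA1c outcomes at weeks 12 and 24, the membership of the subgroup above 9% (which depends on the HbA1c value used), and uniform eligibility at the two sites. The primary outcome, its power and the fairness of the comparison between arms are untouched. The size of any dilution cannot be derived from the documents. The conclusion rests on reading the two time clauses as alternatives and on participation falling on or after the screening date. It is worth correcting, because a stated entry rule is contradictory and the repair is cheap.

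**What to change.** 1. **Eligibility criteria.** Reconcile the two clauses into one time window with one reference date, and define that date. State whether the visit 1 HbA1c is the qualifying value. Both parts are needed: a window of three months before screening would remove the contradiction but could still admit a patient below 8.0% at visit 1. The choice of window is the sponsor's.
2. **HbA1c outcomes at weeks 12 and 24.** Adjust for visit 1 HbA1c together with the two stratification factors: analysis of covariance for the level, and logistic regression for the below-7% outcome. Visit 1 precedes randomization, so this is a proper baseline covariate.
3. **Sensitivity analysis.** Repeat the below-7% outcome in patients whose visit 1 HbA1c was 7% or more. This also covers patients already enrolled under the present wording.
4. **Subgroup above 9%.** State that it uses the visit 1 value, or which other value it uses.

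Cost: a one-line amendment and a little more analysis, with no new data collection. If the visit 1 result is made the qualifying value, recruitment may slow slightly. The restricted analysis will have fewer patients and should be read as supportive only.
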